### Sample size and statistical analysis

The study design is a non-randomized, open-label, cluster intervention. All experimental units (GPs and/or patients) in each cluster receive the scheduled treatment. Assuming that at least 40% of resident in the involved LHUs of the two regions (1.1 million in Lombardy and 1.3 million in Campania) receive at least one prescription during 1-year period, considering a type I error of 5%, a power of 80% would allow to detect, at LHU level, a difference in the reduction of inappropriateness prevalence of at least 5% between intervention and control group.

#### Analysis of indicators

The indicators of performance and of inappropriate prescribing will be determined at baseline and after the intervention, by measuring the explicit indicators defined above within each GP on 1-year base. The unit of analysis will be the patient or his/her prescriptions, depending on the indicator, and GP identified as the clustering factor within each indicator will be examined.

The performance indicators will be evaluated separately on the subpopulations of 40–64 years and ≥65 years. Polytherapy will be evaluated as the percentage of patients with 5–9 drugs or with ≥10 drugs on total GP’s subjects in each age class. Prescription of selected drug classes (as listed above) will be evaluated as percentage of patients on each treatment on total GP’s subjects in each age class and as amount of DDD prescribed per 1000 inhabitants/die in each age class.

Regarding APIs, pDDIs and TDs will be evaluated on subjects ≥40 years old, while drugs in EDR list, ACB scale, and the SL score will be evaluated on subjects ≥65 years old. For each API, the percentage of patients with at least one prescription meeting the API criteria on total GP’s subjects in the specific age class will be determined.

Adherence will be calculated by selecting all patients with a first prescription for the medication of interest within 1-year period. Patients will be required not to have prior prescription of that drug in the year before the index date (defined as the date of the first prescription fill in the period for the selected therapy), to select only incident users. Patients will also be required to have 1 year of enrolment after the index date to allow complete adherence evaluation at 1 year of follow-up.

#### Identification of determinants of inappropriate prescribing

A multilevel model will be considered to identify the association between several variables (related to patients, physicians, or LHUs) and the composite API. The model will allow to take into account the hierarchical structure of the data, with patients nested within physicians and physicians nested within LHU. The considered potential determinants will be measured at the patient level (age, sex, clinical profile using the Chronic Disease Score (Vonkorff *et al*., 1992), and number of prescriptions received), at the physician level (age, sex, and number of patients assisted), and at the LHU level (inhabitants, population density, and number of GPs per 1000 inhabitants).

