Only in the elderly population (aged ≥65 years), we defined the ERD-list (EDU.RE.DRUG list, Table S2 in Supplementary material) developed based on the updated Beers criteria (Radcliff *et al*., 2015), the STOPP&START criteria (O’ Mahony *et al*., 2018), and the EU-(7)-PIM list (Renom-Guiteras *et al*., 2015). The three lists were merged and adapted to Italian setting by selecting only drugs available on the Italian market and reimbursed by Italian NHS. Moreover, the selection was limited to drugs always to be avoided in elderly patients, excluding drugs that should be used with caution or avoided in certain patients with certain diseases or conditions, as these circumstances cannot be evaluated through administrative databases.

The appropriate prescribing indicators (APIs) in elderly comprised also high scores (≥3) of the Anticholinergic Cognitive Burden (ACB) scale (Boustani *et al*., 2008) and of the Sedative Load (SL) score (Linjakumpu *et al*., 2003) from the published lists, again selecting only drugs available on the Italian market and reimbursed by Italian NHS.

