### Study outcome

The study outcome was a composite outcome of API of ERD list, pDDIs, and TDs. The primary end point was therefore defined as the variation of the median prevalence of the composite API after the intervention in the groups with the intervention on GPs (A+B arms) compared to baseline. The prevalence will be calculated at GP’s individual level as the ratio between subjects with the composite API and total GP’s over-40-year subjects.

The secondary end points comprised the (1) variation of the median prevalence of each single API and performance indicator after the intervention, (2) evaluation of difference in efficacy among different types of intervention, (3) identification of predictors of poor prescription appropriateness, (4) health technology assessment (HTA) of intervention implemented, and (5) level of GP satisfaction assessed through an ad hoc web-based questionnaire.

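### The determinants model regresses the composite API on patient age, but the composite gains a third component at age 65, so part of any age effect comes from the outcome definition

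*Protocol article*

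**What the plan says.** Four statements in the protocol article bear on this.

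- *Study outcome* defines the composite: "The study outcome was a composite outcome of API of ERD list, pDDIs, and TDs". Its prevalence is taken over all of a GP's subjects over 40, so both age classes are pooled. Finding predictors of poor appropriateness is secondary end point (3).
- *Definition of inappropriate prescribing indicators* restricts one component by age: "Only in the elderly population (aged ≥65 years), we defined the ERD-list".
- *Analysis of indicators* repeats the restriction: pDDIs and TDs are assessed from age 40, "while drugs in EDR list, ACB scale, and the SL score will be evaluated on subjects ≥65 years old". (The list is spelt EDR there; I take it to be the same list.)
- *Identification of determinants of inappropriate prescribing* makes the composite the outcome of the model: "A multilevel model will be considered to identify the association between several variables (related to patients, physicians, or LHUs) and the composite API". It then lists the predictors: "The considered potential determinants will be measured at the patient level (age, sex, clinical profile" by Chronic Disease Score, and number of prescriptions), followed by GP and LHU characteristics. It states no age restriction, no stratification and no coding of age.

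Elsewhere the plan does split at 65, but only for another set of measures: "The performance indicators will be evaluated separately on the subpopulations of 40–64 years and ≥65 years".

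**The concern.** One of the predictors decides which outcome definition applies to a patient. Suppose two patients, aged 64 and 66, receive the same single ERD-list drug and have neither a pDDI nor a TD. The first is scored as free of the composite API and the second as having it. The model then reports an age association that the definition has partly put there.

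The coefficients of Chronic Disease Score and number of prescriptions have a related difficulty. Below 65 they describe the association with pDDI or TD. From 65 they describe the association with ERD list, pDDI or TD. A pooled coefficient averages the two.

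*Expected results and impact* says the predictors will help set priorities for action and direct scarce resources. A coefficient that mixes definition with prescribing is a poor guide for that.

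**Working it through.** **Structure (no assumptions needed).** From the sections above, the outcome scored is:

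- age 40–64: pDDI or TD;
- age 65 and over: ERD list or pDDI or TD.

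Both groups enter one model with age as a predictor.

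**Inputs for the size.** The protocol gives no prevalence for the composite or its components, so there is no stated figure to reproduce.

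- *b*, prevalence of pDDI or TD: assumed 10% in both age classes, so there is no true age effect on the shared components. Range tried: 5–20%.
- *e*, ERD-list prevalence at 65 and over: 18% (two Italian cohort studies) to 27% (Italy in the European survey), both from the *Rationale*. These are prevalences of potentially inappropriate medication under other definitions, so they are only a proxy.

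**Step at 65 if the components are independent.** Composite at 65+ = 1 − (1 − b)(1 − e).

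- e = 18%: 1 − 0.90 × 0.82 = 0.262; OR against 0.10 = (0.262/0.738)/(0.10/0.90) = 3.2.
- e = 27%: 1 − 0.90 × 0.73 = 0.343; OR = (0.343/0.657)/(0.10/0.90) = 4.7.

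**Step at maximal overlap.** Composite at 65+ = the larger of b and e.

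- e = 18%: OR = (0.18/0.82)/(0.10/0.90) = 2.0.
- e = 27%: OR = (0.27/0.73)/(0.10/0.90) = 3.3.

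**Sensitivity to b, under independence.**

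- b = 5%, e = 27%: 0.3065 against 0.05, a step of about 26 percentage points, OR 8.4.
- b = 20%, e = 18%: 0.344 against 0.20, a step of about 14 points, OR 2.1.
- In the last case maximal overlap would leave the composite at 20% and remove the step (OR 1.0), because every patient with an ERD-list drug would already count.

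**If pDDI/TD truly rises with age**, say 10% to 15%, the like-for-like OR is (0.15/0.85)/(0.10/0.90) = 1.6. The composite under independence is 0.303–0.380, giving OR 3.9–5.5.

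**Effect inside a regression.** I used simulated data: 400,000 patients aged 40–95, 38% aged 65 or over (assumed), one covariate with no true effect, and ordinary logistic models without random effects. The pairs (b, e) were (10%, 18%), (5%, 27%) and (20%, 18%).

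| Quantity | OR |
|---|---|
| Age per decade, linear age, composite outcome (truth 1.00) | 1.23–1.91 |
| Null covariate, linearly related to age | 1.00–1.01 |
| Null covariate (per SD), rising in an S-shape around 65 | 1.04–1.12 |
| Null covariate, convex in age | 0.91–0.99 |
| Age per decade after adding a 65-and-over term | 0.99–1.02 |
| The 65-and-over term itself | 2.1–8.4 |
| Age per decade, outcome pDDI or TD only | 0.99–1.01 |

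A break at 65 cleans the age slope and the null covariate, but the break term then carries the step. Restricting the outcome to the shared components removes it.

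**The case against.** **The age limit is the construct.** The ERD list holds drugs always to be avoided in the elderly, so the same drug really is inappropriate at 66 and not at 64 under these criteria. That is a sound definition, and higher composite risk in the elderly is then a true statement about the defined outcome. What remains is interpretation: the pooled coefficient cannot separate that definition from a difference in prescribing, and it is to be reported as a determinant.

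**Coding of age belongs in an analysis plan.** This is right, and its absence from an article is no fault. But the step enters the age effect however age is coded. It arises from the stated outcome and the stated predictor list together.

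**The size is fragile.** This stands. The pDDI/TD prevalence is assumed, the ERD figures are a proxy, and the odds ratios are crude, whereas the planned model adjusts for disease score and number of prescriptions.

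**Stronger readings that the protocol does not support.**

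- A reader might infer that the step leaks into every age-related covariate. Age is in the model, so leakage needs both age coded without a break at 65 and a covariate that is non-linear in age. Even then it was small and could take either sign.
- A reader might infer that age must emerge as the leading determinant whatever GPs do. If no ERD-list drugs were prescribed to the elderly, e would be 0 and the step would vanish. The effects of disease score and number of prescriptions are unknown and could be larger.
- A reader might infer that GP or LHU effects are distorted. Nothing here shows that.

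**Conclusion.** The point holds in a limited form. As written, the determinants analysis gives an age effect that mixes the change in outcome definition at 65 with any real difference in prescribing. The structural part follows from the text alone, provided ERD-list drugs are prescribed to some elderly patients who have no pDDI or TD. The illustrative size is a crude age-group OR of about 2.0 (maximal overlap, ERD 18%) to 4.7 (independence, ERD 27%), with pDDI/TD assumed at 10% in both classes and no true age effect on the shared components. Other assumed values of pDDI/TD widen that range in both directions.

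The pooled coefficients of Chronic Disease Score and number of prescriptions also average over two outcomes. Leakage into other covariates is at most small. The scope is secondary end point (3); the primary pre-post comparison is not at issue. The change is worth making because the predictors are meant to guide action and the remedy is cheap.

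**What to change.** In *Identification of determinants of inappropriate prescribing*, state that the model will be fitted separately in the two age classes already used in *Analysis of indicators*:

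- 40–64 years, outcome pDDI or TD;
- 65 years and over, outcome the full composite (ERD list, pDDI or TD).

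If an all-ages model is also reported, either use pDDI or TD as its outcome, or include a 65-and-over term with interactions and say that this term is not interpreted as a determinant. An all-ages model on pDDI or TD leaves out the elderly-specific component, so it should supplement the stratified models and not replace them.

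The cost is a change of wording and one more results table. The small downside is two sets of coefficients to present. No new data are needed.

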#### Interventions effectiveness (pre-post analysis)

The primary and secondary outcomes will be evaluated in a 6-month period before intervention (pre-intervention phase, October 2016–March 2017) and in a 6-month period after the intervention (post-intervention phase, October 2018–March 2019). Depending on LHU and on type of data, administrative data usually require 3–6 months to be processed and made available. The difference (Δ pre-post) in the outcomes will be estimated separately for each LHU. Appropriate contrasts to compare Δ in the different groups of intervention and the corresponding confidence intervals will be estimated. The standard error for each contrast will be assessed by an appropriate normality assumption or, if this assumption is not plausible, by other methods such as the nonparametric bootstrap.

Since the study is not randomized, to consider the potential confounding due to physicians’ and patient’s characteristics, two additional analyses will be made at physician and patient level. Firstly, the Δ of each physician will be evaluated. A linear mixed regression model will be applied including the Δ as response variable and physicians and the LHU characteristics as well as the type of intervention as covariates. To take into account that physicians are clustered within LHU, a random effect for LHU will be considered. A generalized linear mixed regression model considering post-intervention prevalence of composite API as response variable will be estimated. In this model, patient-, physician-, or LHU-level covariates will be included. Two random effects will be considered in the model: one for the physician and one for the LHU. To take into account the baseline probability of being inappropriately treated, we will include in the model the prevalence of composite API for the patient’s physician evaluated before the intervention.

To evaluate the effects of interventions in terms of the subsequent mortality risk, all patients receiving at least one prescription during the post-phase will be selected and followed for 1 year. The vital status of each patient will be recorded during the year. A Cox proportional hazard regression model will be applied to evaluate the association between the intervention and mortality. The response variable will be the time to death and the model will include different covariates measured at the patient-, physician-, and LHU-level, the type of intervention, and the prevalence of composite API for the physician assigned to each patient as evaluated before the intervention.

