**Methods and analysis::**

This is a prospective, multicentre, open-label, parallel-arm, controlled, pragmatic trial directed to GPs and their patients in two Italian regions (Campania and Lombardy). The study data are retrieved from administrative databases (Demographic, Pharmacy-refill, and Hospitalization databases) containing healthcare information of all beneficiaries of the National Health Service in the Local Health Units (LHUs) involved. According to LHU, the GPs/patients will be assigned to one of the following four intervention arms: (1) intervention on GPs and patients; (2) intervention on GPs; (3) intervention on patients; and (4) no intervention (control). The intervention designed for GPs consists of reports regarding the status of their patients according to the APIs determined at baseline and in two on-line Continuous Medical Education (CME) courses. The intervention designed for patients consists in flyers and posters distributed in GPs ambulatories and community pharmacies, focusing on correct drug use.

A set of indicators (such as potential drug–drug interactions, unnecessary duplicate prescriptions, and inappropriate prescriptions in the elderly), adapted to the Italian setting, has been defined to determine inappropriate prescription at baseline and after the intervention phase. The primary outcome was a composite API.

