### Study intervention

The GPs and their patients have been assigned to one of the following arms (Figure 1):A: intervention on GPs and patients (LHUs of Napoli 2 Nord and Lecco);B: intervention on GPs (LHUs of Napoli 1 Centro and Bergamo);C: intervention on patients (LHUs of Avellino and Mantova);D: control group (LHUs of Caserta and Monza Brianza).

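### The between-arm contrasts of Δ state no standard error that carries LHU-to-LHU variation, although the LHU is the unit of assignment and each arm has only two

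*Protocol article*

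**What the plan says.** The abstract of the protocol article makes the LHU the unit of assignment: "According to LHU, the GPs/patients will be assigned to one of the following four intervention arms". The section Study intervention places two LHUs, one from each region, in every arm. Arm A comes first in "intervention on GPs and patients (LHUs of Napoli 2 Nord and Lecco);B: intervention on GPs (LHUs of Napoli 1 Centro and Bergamo", and arms C and D follow in "intervention on patients (LHUs of Avellino and Mantova);D: control group (LHUs of Caserta and Monza Brianza". The sample size section describes the design as follows: "The study design is a non-randomized, open-label, cluster intervention. All experimental units (GPs and/or patients) in each cluster receive the scheduled treatment".

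The section Interventions effectiveness (pre-post analysis) then sets out the estimate: "The difference (Δ pre-post) in the outcomes will be estimated separately for each LHU". Contrasts between intervention groups follow, with confidence intervals, and on their precision the plan says: "The standard error for each contrast will be assessed by an appropriate normality assumption or, if this assumption is not plausible", by alternatives of which the bootstrap is the example given. No level of variance and no resampling unit is named.

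The section Analysis of indicators takes the patient or the prescription as unit of analysis, with "GP identified as the clustering factor within each indicator will be examined". In the effectiveness section, a random effect for LHU is specified for two further models, one at physician level and one at patient level. Both are introduced as additional analyses to deal with confounding.

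**The concern.** LHUs can change over two years for local reasons unrelated to the interventions, such as formularies, budgets and prescribing programmes. With two LHUs per arm, such changes do not average out, and they may be the largest source of uncertainty in any comparison of arms. A standard error attached to a Δ estimated inside one LHU reflects only the spread among that LHU's GPs or patients. Adding such errors across LHUs, or bootstrapping GPs within LHUs, does not bring the missing component back. An ordinary local difference could then be reported as an intervention effect with a tight interval.

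This bears on the comparisons between arms: secondary end point (2), and the intervention-versus-control difference in the power statement. The primary end point in Study outcome is a pre-post change within A+B, and the argument here does not concern it.

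**Working it through.** **The plan's own figure.** The head counts reproduce: 0.4 × 2.8 million = 1.12 million and 0.4 × 3.3 million = 1.32 million, against the stated 1.1 and 1.3 million. The claim of 80% power for 5%, at LHU level, does not follow from those counts. I read 5% as percentage points and assume baselines of 10–50%.
- With 1.2 million independent patients per side (A+B v C+D), power is essentially 100%. The difference detectable with 80% power is 0.11–0.18 points, or 0.15–0.26 for a difference in differences.
- For 5 points, 906 patients per group suffice at a 20% baseline and 1,565 at 50%.
- Analysed by LHU, 80% power holds if the between-LHU SD of Δ is about 2.1 points (4 v 4 LHUs, 6 df), 1.3 (2 v 2, variance pooled over four arms, 4 df) or 0.9 (2 v 2, 2 df).

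So the power statement turns on the same between-LHU variance that the contrasts do not mention.

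**Reading 1: the standard error comes from GPs within LHUs.** Let m be GPs per LHU and ρ the share of the variance of GP-level Δ that lies between LHUs. Then, approximately,

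true SE / GP-level SE = √(1 + (m − 1)ρ).

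Neither m nor ρ is in the article. Assuming 1,000–1,500 residents per GP, 6.1 million residents give about 4,100–6,100 GPs, or roughly 510–760 per LHU. The table uses m = 500 and LHUs of equal size. Type I error is simulated for the nominal 5% test, 4 v 4 LHUs.

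| ρ | SE ratio | Type I error |
|---|---|---|
| 0 | 1.00 | 5% |
| 0.001 | 1.22 | 11% |
| 0.005 | 1.87 | 30% |
| 0.01 | 2.45 | 43% |
| 0.02 | 3.31 | 56% |
| 0.05 | 5.09 | 71% |

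Example: √(1 + 499 × 0.01) = √5.99 = 2.45. For m = 200, the ratio runs from 1.09 (ρ = 0.001) to 3.31 (ρ = 0.05); for m = 800, from 1.34 to 6.40. A doubling of the SE needs ρ = 3/(m − 1), which is 0.015, 0.006 or 0.004 for m = 200, 500 or 800.

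**The same reading in percentage points.** Assume G = 4,100–6,100 GPs in all, an SD of GP-level Δ of 4–6 points and a between-LHU SD of Δ of τ.
- GP-level SE = SD × √(2/(G/2)) = 0.10 to 0.19 points.
- True SE = √(GP-level SE² + τ²(1/4 + 1/4)).
- τ = 0.5: true SE 0.37–0.40, ratio 2.1–3.6, type I error 36–59%.
- τ = 0.25: ratio about 1.4–2.0, type I error 15–33%.
- τ = 1: type I error 61–78%.

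**Reading 2: the standard error comes from the LHUs.** Between-LHU variation is then included, but two problems remain.
- Limits of ±1.96 are too short for so few units. The t values are 2.447 (6 df), 2.776 (4 df) and 4.303 (2 df), so correct intervals are 1.25, 1.42 and 2.20 times as wide.
- Resampling two LHUs within an arm gives three distinct resamples. The expected bootstrap variance is (2 − 1)/2 = one half of the unbiased value. With normal limits as well, the shortfall against 4 df is 1.42 × √2 = 2.0. Each arm has one LHU per region, so a bootstrap stratified by region has nothing to resample.

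**The case against.** The strongest reply is that the plan never says its standard errors are GP-based. The sentence on the contrasts leaves the level open, and a Δ for each LHU is exactly what an LHU-level analysis would start from. The phrase on GP clustering sits in the section on measuring the indicators, and the power statement refers to the LHU level. A reader might infer that the contrasts are fixed at GP level and that the intervals will certainly be several times too narrow. The document supports neither. The first is a plausible inference, helped by the fact that normality cannot be judged from two LHUs per arm. The second needs a GP count and variances that the article does not give; at ρ = 0.001 and m = 500 the SE ratio is only 1.2.

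It is also true that the plan recognises the LHU. Both additional models carry an LHU random effect, and the model for determinants nests physicians within LHUs. In a non-randomised study those adjusted models may well carry much of the interpretation. This stands, but it shows the plan applying the LHU level in the supporting models while stating none for the contrasts they support.

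Finally, a resampling unit or degrees of freedom may properly be left to an analysis plan. Silence on those alone would be no finding. Here, however, the article does state how the standard error will be obtained, and the methods it names understate uncertainty under Reading 1 whenever LHUs differ in change, and under Reading 2 because there are so few LHUs.

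**Conclusion.** The concern holds in a conditional form. The between-arm contrasts state no between-LHU variance although treatment follows the LHU. The direction of the error is clear: intervals too short and type I error above 5%. Its size cannot be derived from the article. With the assumed 500 GPs per LHU and ρ from 0.001 to 0.05, the true SE is about 1.2 to 5 times the GP-level SE and the type I error about 11% to 71%. If the contrasts are already LHU-based, what remains is the small-sample problem of normal limits and of bootstrapping two units per arm. A several-fold error is possible but not established.

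**What to change.** For every between-arm comparison, state that the LHU is the unit of inference, by one of two routes:
- Analyse the eight LHU-level Δs with region as a factor, using the residual variance between LHUs and t limits on the residual degrees of freedom. Four separate arms plus region leave 8 − 5 = 3 df. An additive model (GP intervention, patient intervention, region) leaves 8 − 4 = 4 df, critical value 2.776; if it is used, say that it assumes no interaction between the two interventions, so it cannot show whether the combination does more than the sum of its parts.
- Or make the planned physician-level mixed model of Δ, with its LHU random effect, the main contrast, with small-sample degrees of freedom. Each LHU-level covariate uses up one of these few degrees of freedom, so such covariates must be kept to a minimum.

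Rule out a GP- or patient-level bootstrap for these contrasts, and also a cluster bootstrap of two LHUs per arm. Where the GP is named as clustering factor, say that for between-arm comparisons GPs are nested in LHUs.

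The cost is a change of analysis wording and no new data. Intervals will be wider, and the power statement must be checked against the LHU-level analysis, with the assumed between-LHU SD of Δ written down.

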### Data source and collection

In Italy, National Health Service (NHS) provides universal coverage largely free of charge at the point of delivery. The regions are responsible for organizing and delivering healthcare through the LHUs. The study data are retrieved from administrative databases containing healthcare data of all beneficiaries of the NHS in the LHUs involved: in 2017, about 2,800,000 beneficiaries for the 4 LHUs in Lombardy (Bergamo, Lecco, Mantova, and Monza Brianza) and 3,300,000 beneficiaries for the 4 LHUs in Campania (Avellino, Caserta, Napoli 1 Centro, and Napoli 2 Nord) (ISTAT, 1999). These databases, set up and constantly updated by regional or local health authorities, are:Demographic Databases, containing data on residents who receive NHS assistance (birth date and sex), and on GPs (birth date, sex, and number of patients).Pharmacy-refill Databases, containing data on drug prescriptions reimbursable by the NHS, including prescription date, dispensation date, the Anatomical Therapeutic Chemical (ATC) classification, marketing authorization code, number of boxes, and cost for NHS.Hospitalization Databases, containing data on hospital discharge at public or private hospitals of the regions, including the admission date, the primary and secondary diagnoses, and the date of discharge.

Compliance with national and European laws on personal data is guaranteed by LHUs through the generation of unique anonymous codes for each patient and each prescriber, providing guarantees in respect of the privacy of every citizen.

Data used in this project cover a time period ranging between the years 2014–2017 (baseline) and 2018–2019 (follow-up).

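### The patient-level model uses the GP's average as its baseline term, which cannot correct for patient turnover that differs between LHUs; the patient's own baseline status should be added beside it (minor)

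*Protocol article*

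**What the plan says.** The point concerns the protocol article, section Interventions effectiveness (pre-post analysis). The main analysis there estimates the pre-post difference for each LHU and contrasts it between intervention groups. Because allocation was not random, "two additional analyses will be made at physician and patient level".

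The patient-level one is described in these words: "A generalized linear mixed regression model considering post-intervention prevalence of composite API as response variable will be estimated". On adjustment it says "In this model, patient-, physician-, or LHU-level covariates will be included", without listing them, and "Two random effects will be considered in the model: one for the physician and one for the LHU". The baseline term is introduced by its purpose, "To take into account the baseline probability of being inappropriately treated, we will include in the model the prevalence of composite API", and is then defined as "the prevalence of composite API for the patient’s physician evaluated before the intervention".

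Two other places matter. Under Study outcome, a GP's prevalence is the number of subjects with the composite indicator divided by all of the GP's subjects over 40. Under Data source and collection, the LHUs ensure privacy through "the generation of unique anonymous codes for each patient and each prescriber".

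The response is worded as a prevalence. I read it as each patient's composite status, since the model is announced as patient-level and carries a physician random effect.

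**The concern.** The purpose given for the baseline term is individual: how likely a patient was to be inappropriately treated before the intervention. The term chosen is a list average and cannot separate two patients of the same GP. Yet each patient's pre-window status has to be classified before that average can be computed, and patient codes appear to allow it to be carried to the post window.

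What is at stake is confounding control, which is the reason the protocol gives for this model. The windows (October 2016-March 2017 and October 2018-March 2019) are two years apart and the population is everyone aged 40 or over. In between, patients die, move, change GP or turn 40. The GP's pre-window average describes the old list, while the response comes from the new one. If turnover differs between LHUs, the average cannot correct for it.

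**Working it through.** The protocol gives no figure for this adjustment, so there is none to reproduce. It also gives no baseline prevalence, between-GP variance, within-patient correlation or turnover rate. All values for these below are assumptions.

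**Step 1. Does the GP average describe the individual?** Simulation: 8 LHUs (4 treated, 4 untreated), 60 GPs per LHU, 400 patients per GP, the same patients in both windows, true effect zero, 60 replicates per scenario. Assumed logit SDs: LHU 0.1, GP 0.3-0.6, patient 2-3; LHU-level change 0-0.1. Share of variance explained:

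- GP prevalence on a patient's own baseline status: 1.0-3.6%.
- GP prevalence on post-window status: 0.8-3.4%.
- Own baseline status on post-window status: 15-29%.

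The GP average is a weak proxy for one patient's risk.

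**Step 2. Does that harm the arm contrast when the list is stable?** Let y0 be a patient's baseline status and m the GP mean of y0. Within each GP the sum of (y0 - m) is zero. Arm and m are constant within a GP, so (y0 - m) is orthogonal to both. In a linear model that already contains m, adding y0 therefore cannot move the arm coefficient. The same simulation, with a 0.4-logit case-mix shift between arms, gave these arm coefficients in percentage points (true value 0):

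| Baseline term | Range over scenarios |
|---|---|
| None | 4.3 to 5.8 |
| GP prevalence | 0.3 to 0.8 |
| Own status only | 2.0 to 3.6 |
| GP prevalence and own status | 0.3 to 0.8 |

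Bias removed by the GP term: (5.84 - 0.82)/5.84 = 86% at the low end and (5.61 - 0.26)/5.61 = 95% at the high end. Adding own status left both the mean and the between-replicate SD unchanged (0.77 and 1.375 points in both models in one scenario). Replacing the GP term with own status left more bias, because one binary observation measures a patient's propensity with error.

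**Step 3. What if the list is open?** Suppose joiners make up a share s of the post-window list, their risk differs from the GP mean by g, and leavers are a random sample of the list. The GP's pre-window average misses s x g, so the arm contrast is biased by (difference in s) x g:

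- 0.02 x 0.10 = 0.002, or 0.2 points.
- 0.05 x 0.20 = 0.010, or 1.0 point.

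An open-cohort simulation checks this: same numbers of LHUs, GPs and patients, linear model, true effect zero, no LHU-level change, 40 replicates. It assumed 10% turnover, 2-5 points higher in one arm, and joiners 1-2 logits lower in risk. Bias in the arm coefficient, in points:

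| Assumption | GP term only | GP term and own status (yes / no / not observed) |
|---|---|---|
| 5-point turnover difference, random leavers | -0.47 to -0.96 | +0.07 to -0.04 |
| 5-point turnover difference, higher-risk leavers | -1.65 to -1.93 | -0.79 to -0.88 |
| 2-point turnover difference | -0.10 to -0.80 | +0.12 to -0.33 |

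In the mildest case there was no gain (-0.10 against +0.12). A separate simulation with random leavers and a 2-5 point difference gave about -0.2 to -1.0 with the GP term alone, and 0 to 0.1 in size after own status was added. The SD of the arm coefficient was again essentially unchanged.

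**The case against.** The strongest reply is that arms are whole LHUs, so what matters is balance between groups of lists, and a list average is the right kind of variable for that. Step 2 shows this is correct for a stable list.

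A reader might also infer that leaving out own status costs precision. It does not, in any way that matters. The Sample size section gives 1.1 + 1.3 = 2.4 million people, or 600,000 per arm if split evenly over four arms. At an assumed prevalence of 30%, the patient-level standard error of a two-arm difference is sqrt(2 x 0.3 x 0.7 / 600,000) = 0.08 points. Own status with an assumed pre-post correlation of 0.3-0.6 would cut that by 5-20%, or 0.004-0.017 points. The uncertainty lies between LHUs, two per arm, and own status does not reduce it.

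Further, the model does contain patient-level covariates. They are not itemised, and a condensed article may leave the list to a fuller plan. If age and clinical profile are among them, they would absorb part of the turnover bias. This stands as a reason for caution, but the article itself names the baseline term and its purpose, and those two do not match.

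It is also fair to say that joiners without a pre-window record have no own status, so the not-observed category does much of the work. That is why the fix needs three levels, and it does not weaken the point.

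Two other inferences go beyond the documents. The mortality Cox model uses the same term, "the prevalence of composite API for the physician assigned to each patient as evaluated before the intervention", but nothing here shows that own baseline status would alter that comparison. And a main-effect covariate would not show whether the intervention resolves existing inappropriate prescribing or prevents new cases; that needs an arm-by-baseline-status interaction.

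**Conclusion.** The point holds in a limited form. The named baseline term is contextual and is not the individual probability it is said to represent. For a closed list that mismatch is harmless to the arm contrast. For the open population actually studied, it leaves about 0.2-1.0 points of bias under an assumed 2-5 point difference between arms in turnover with joiners 10-20 points off the GP mean, and up to 1.9 points in the scenarios with higher-risk leavers. No turnover figures are given, so the true size is unknown and could be negligible.

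For scale, if the 5% difference in the Sample size section is read as absolute points (the text does not say), 0.2-1.0 points is 0.2/5 = 4% to 1.0/5 = 20% of it.

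The results come from linear models; a logistic link would change the scale of the arm effect. Severity is minor: the model is one of two additional analyses, and the main contrast of pre-post differences by LHU does not depend on this covariate.

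**What to change.** In the patient-level mixed model:

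- Keep the GP's pre-intervention prevalence, described as a contextual covariate, and keep both random effects.
- Add the patient's own composite status in October 2016-March 2017 as a patient-level covariate with three levels: yes, no, not observed. Add it beside the GP term, not in its place, since own status alone left 2.0-3.6 points of bias in step 2.
- State the response as the patient's composite status in the post window, so that a patient-level covariate fits the model as written.
- If the sponsor wants to separate resolution of existing cases from prevention of new ones, specify an arm-by-baseline-status interaction for that purpose.

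The cost is a wording change and one covariate, derivable from statuses already classified for the GP prevalence and from the patient codes. No new data are needed.
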